### 2.3. Participants

All under-4 children and their mothers/caretakers, resident in the selected hamlets, will be considered eligible and invited to participate. This age group was selected because children are expected to have limited mobility, to receive higher parental attention and to have their exposure to contaminated environments more controllable than school aged children. Children will be subject to exclusion whenever having recently received blood transfusions, report adverse reactions to albendazole and/or to praziquantel, and when their caretakers do not commit to completing both the evaluation and the educational moments of the study. Only children with pre-intervention evaluation will be allocated to the Randomized Controlled Trial (RCT).

### 2.4. Training for Evaluation Moments

At the beginning of the study, 6 field workers and 2 nursing technicians will be selected from the study area and trained. The one-week training will incorporate: (1) an introduction to the research questions, goals and study design; (2) basic concepts regarding the diseases studied; (3) methodologies for data collection (structured interviews, anthropometric evaluations, recognition of signs and symptoms of micronutrient deficiency, measurement of temperature); and (4) communication skills and the collection/delivery of information. Additionally, nursing technicians will undergo 3-day training on: (1) the treatment and referral protocol adopted in this study; (2) best practices for drug administration in young children; and (3) the management of domiciliary and health unit treatments. Blood, urine and stool samples will be collected before their processing by experienced CISA resident laboratory technicians. A field work simulation class will be conducted with all personnel involved in this survey at the end of all training sessions.

### 2.5. Recruitment of Participants

A house-to-house recruitment team will identify the children eligible in each hamlet, explaining the importance of the study both to local authorities and caretakers, delivering stool and urine containers and explaining the best practices for sample collection. This team will recruit up to 45 children per day, and orient them to attend the next evaluation at the hamlet health post. Those evaluations will be carried out in each hamlet until all eligible willing-to-participate families have been notified.

### 2.6. Baseline Data Collection and Sample Storage

A structured questionnaire is to be administered to mothers or other primary caretakers to collect information on identification, breastfeeding, complementary feeding practices and health care practices, supplementation and vaccination history, WASH and malaria practices. Weight and height, collected using electronic or platform pediatric scales and measuring harness or adult stadiometer, will be used to calculate anthropometric indices for the diagnosis of undernutrition in children and mothers according to WHO standards [45,46]. Peripheral blood will be collected in accordance with WHO good phlebotomy practices [47]. For biochemical analyses, blood will be collected in 1.1ml Z-Gel microvette tubes, centrifuged for the separation of the serum and stored at −20 °C and blood for molecular analysis will be stored in air-dried filter paper until processing. Mothers/caretakers will be instructed to collect a stool sample on the day before evaluation and to collect urine in the morning of evaluation day. Urine samples are to be conserved in formalin (10%) to prevent larvae eclosion.

### 2.7. Sample Processing

Stool, urine and blood will be analyzed parasitologically. Blood protozoa (*Plasmodium falciparum* and *Plasmodium vivax*) will be determined by the Rapid diagnostic test (*SD BIOLINE* Malaria Ag P.f/P.v (HRP-2/pLDH, Standard Diagnostics, INC, Suwon City, Korea))*,* intestinal helminths (*Ascaris lumbricoides, Trichuris trichiura*, *Hymenolepis nana* and *Strongyloide stercoralis*) determined through fecal smear according to the Katokatz technique, intestinal protozoa (*Giardia lamblia* and *Entamoeba hystolitica/dispar*) evaluated through fecal centrifugal-sedimentation (using Parasitrap® System, Biosepar, Mühldorf, Germany) and urogenital helminth (*Schistosoma haematobium*) determined by urine filtration [48,49]. Biochemical analyses will comprise quantifying hemoglobin directly from peripheral blood (using Hemocue ® Hb 301 System, Angelholm, Sweden), serum ferritin, C-reactive protein and zinc through kits from Quimica Clínica Aplicada (Quimica Clínica Aplicada S.A., Tarragona, Spain) and an automated analyzer (BT1500, Biotecnica Instruments S.p.A, Rome, Italy), serum retinol through high-performance liquid chromatography with a protodiode-array detection, and vitamin B12 and folic acid by chemiluminescence immunoassay (using VITROS® Immunodiagnostic kits, Ortho Clinical Diagnostics, Inc. Bridgend, UK) [50,51,52,53]. Molecular analysis will include DNA extraction (by Chelex method), screening for sickle cell trait and disease (by PCR) and G6PD deficiency (by rtPCR) [54,55]. Malaria diagnosis will take place on site, and stool/urine samples will be analyzed within 24/48 h of collection (depending on the day of the week). The laboratory analyses will be performed by trained technicians and 25% of tests subject to confirmation by experienced laboratory supervisors.

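### Kato-Katz is the only method named for Strongyloides stercoralis, so this species will be largely missed within the soil-transmitted helminth secondary outcomes

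*Protocol article*

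**What the plan says.** Section 2.7 (Sample Processing) gives one method per group of organisms.

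- Intestinal helminths, listed as Ascaris lumbricoides, Trichuris trichiura, Hymenolepis nana and Strongyloides, are "determined through fecal smear according to the Katokatz technique".
- Intestinal protozoa (Giardia and Entamoeba) go through a separate fecal centrifugal-sedimentation step.
- S. haematobium is "determined by urine filtration".
- For malaria, "Malaria diagnosis will take place on site", by rapid test.

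On timing, section 2.6 has caretakers "collect a stool sample on the day before evaluation and to collect urine in the morning of evaluation day", and section 2.7 says "stool/urine samples will be analyzed within 24/48 h of collection (depending on the day of the week". Section 2.6 adds a preservation step for urine: "Urine samples are to be conserved in formalin (10%) to prevent larvae eclosion". The article says nothing either way about preserving or cooling stool.

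Table 2 lists prevalence, intensity, incidence and reinfection of STH, P. falciparum and S. haematobium as secondary outcomes. The primary outcomes are hemoglobin and anemia prevalence. Section 2.8 (Drug Therapy) treats children who have been diagnosed. It ties albendazole to Ascaris, Trichuris and hookworms, and praziquantel to the two Schistosoma species and H. nana.

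**The concern.** The method does not fit one of its four named targets. A Kato-Katz smear is read for eggs. Strongyloides is normally shed as larvae, so a smear will usually be negative whether or not the child is infected. The 25% supervisor confirmation in section 2.7 does not help: it catches misreading of a slide, not a technique that does not show the organism.

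The STH outcomes are a direct measure of what the WASH/malaria education is meant to change (section 1.2). A species reported at close to zero in every arm contributes nothing to that comparison. The baseline etiologic profile would also suggest the parasite is nearly absent when it has not been adequately looked for.

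Two smaller matters sit in the same sections. The permitted time to reading varies with the weekday, and the article does not say that the actual interval is recorded. The helminths that section 2.7 diagnoses are also not the ones that section 2.8 treats.

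**Working it through.** **Method against target (section 2.7)**

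| Target | Stage normally found in stool | Method named | Fit |
|---|---|---|---|
| Ascaris, Trichuris, H. nana | eggs | Kato-Katz | suitable |
| Strongyloides | larvae | Kato-Katz | poor |
| Giardia, Entamoeba | protozoan forms | centrifugal sedimentation | separate method |

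The second column is general knowledge of these organisms; the article does not state it. The mismatch is confined to one row.

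**Size.** The article states no sensitivity, prevalence, sample size or power for any infection outcome, so there is no figure to reproduce. What follows is illustration only.

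Assumptions: true Strongyloides prevalence 20% v 10%; specificity 1; the same sensitivity s in both arms; 199 children per arm, which gives 80% power at s = 1; two-sided alpha 0.05; individual-level comparison with no allowance for clustering.

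Observed prevalence = s × true prevalence. Hence the risk difference = s × 10 points, and the risk ratio = (s × 20%) / (s × 10%) = 2.0 for any s. The odds ratio is [a/(1 − a)] / [b/(1 − b)] with a = 0.20s and b = 0.10s.

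| s | Observed | Difference (points) | Risk ratio | Odds ratio | Power |
|---|---|---|---|---|---|
| 1.0 | 20% v 10% | 10 | 2.0 | 2.25 | 80% |
| 0.9 | 18% v 9% | 9 | 2.0 | 2.22 | 75% |
| 0.7 | 14% v 7% | 7 | 2.0 | 2.16 | 63% |
| 0.5 | 10% v 5% | 5 | 2.0 | 2.11 | 47% |
| 0.3 | 6% v 3% | 3 | 2.0 | 2.06 | 30% |
| 0.1 | 2% v 1% | 1 | 2.0 | 2.02 | 13% |

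If an egg-based smear seldom shows a larva-shedding worm, the lower rows are the relevant ones. Ratio measures move little; the loss is in absolute difference and power.

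**Pooled STH outcome.** If any-STH infection is analysed, observed prevalence = true prevalence − (1 − s) × prevalence of Strongyloides without another detected STH. Children with a second, detected STH species still count as infected. The pooled loss is therefore no larger than the Strongyloides-only share, which the documents do not give.

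**Diagnosed against treated (section 2.7 v section 2.8)**

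| Helminth | Listed as diagnosed in 2.7 | Named with a drug in 2.8 |
|---|---|---|
| Ascaris, Trichuris, H. nana, S. haematobium | yes | yes |
| Strongyloides | yes | no |
| Hookworms | no | yes |
| S. mansoni | no | yes |

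Table 1 does not resolve this, because it attaches its drugs to intestinal parasites as a group without naming species.

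**The case against.** The strongest reply is that this matters little. Primary outcomes do not come from stool or urine. Malaria, with the largest infection share of anemia in the Background (16%, against 10% for S. haematobium), is tested on site. The Background gives Strongyloides no share of anemia, and Table 2 names STH as a group with no Strongyloides outcome of its own. Follow-up evaluations repeat the baseline design (section 4), and Table 1 gives all arms the same diagnosis and treatment, so under-detection should be non-differential: it costs power without favoring an arm. All of this stands and limits the point to secondary outcomes. It does not defend Kato-Katz as the sole method for Strongyloides.

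A reader might infer more from these sections. Three such readings are not supported.

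- **That unpreserved stool deteriorates before reading.** The article is silent on stool storage, and a condensed article may leave that to the full protocol. The organism usually cited as delay-sensitive, hookworm, is not a listed target in section 2.7. Nor does anything tie weekday to hamlet or arm: section 2.5 has evaluations continuing in each hamlet until all willing families have been notified.
- **That morning urine loses S. haematobium eggs.** Nothing in the documents bears on the time of egg output. The article fixes a collection time, a preservative and a filtration method.
- **That test-and-treat as a whole rests on false negatives.** Three of the four listed intestinal helminths shed eggs suited to the smear, protozoa have their own method, and malaria has a rapid test. Because section 2.8 names no drug for Strongyloides, the documents do not even show that a missed case would change treatment.

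**Conclusion.** The point holds for one species. Section 2.7 fixes a method that will leave Strongyloides largely undetected, so it will be under-counted in STH prevalence, intensity, incidence and reinfection. The size cannot be set from the documents. At equal sensitivity and perfect specificity, the species-specific risk difference falls to s times the truth, and the effect on any pooled STH measure is bounded by the Strongyloides-only share. This assumes that Strongyloides belongs to the STH group, which Table 2 does not define by species, and rests on general knowledge of the smear and the worm, not on a stated figure.

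It is a modest measurement flaw in secondary outcomes. It does not invalidate the comparison between arms and does not touch the primary outcomes or malaria. The varying stool interval justifies recording it, not a claim of bias. The disagreement between sections 2.7 and 2.8 is plain on the page.

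**What to change.** 1. In section 2.7, remove Strongyloides from the Kato-Katz list and state that larvae are read from the centrifugal-sedimentation preparation already made for protozoa, in all arms and at all three evaluations. The laboratory should first confirm that its kit retains larvae. Define Strongyloides as present or absent, because larval findings are not comparable with egg counts as a measure of intensity. Cost: wording and longer slide reading; no new assay.
2. Record collection and reading times for each stool sample, so that the interval can be described by hamlet, arm and wave. Cost: two fields on the laboratory form.
3. Reconcile sections 2.7 and 2.8 so that organisms listed as diagnosed and as treated correspond, or explain each difference: Strongyloides on one side, hookworms and S. mansoni on the other. Which list should change is for the clinical and laboratory team. In the same edit, state which species make up STH in Table 2.

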### 2.8. Drug Therapy

Children diagnosed with *Plasmodium falciparum* malaria, urogenital schistosomiasis and/or intestinal parasites, will receive treatment, respectively with artemether/lumefantrine (20/120, plus paracetamol (15 mg/kg/dose for temperatures above 38 °C)), albendazol (400 mg/single dose for *Ascaris lumbricoides*, *Trichuris trichiura* and hookworms) and praziquantel (40 mg/kg for *Schistosoma haematobium* and *Schistosoma mansoni* (splited into two intakes, 6 h apart) and 25 mg/kg for *Hymenolepis nana*), according to the national therapeutic guidelines and specialist bibliography [56,57,58,59]. *Plasmodium falciparum*-infected children are to be treated on the evaluation site (unless signs of severe malaria are observed) and all albendazole treatments (except for children aged younger than one) will be administered in the household by nurse technicians. The remaining infected children will be treated at specific consultations with CISA’s pediatrician at the health centers. Furthermore, any children diagnosed with sickle cell disease will be referred to the Anemia Patient Follow-up Consultation, held at the Bengo General Hospital. Drugs will be provided by CISA through the entire duration of the study.

## 3. Cluster-Randomized Controlled Trial

### 3.1. Sampling Strategy

In this study, the sampling strategy chosen was a non-probabilistic (convenient) sampling. In sum, we aimed to include (through a census approach) all eligible children (under the age of 4) resident in administratively and geographically isolated hamlets with functional health posts, in turn located within the CISA’s HDSS study area (considered as cluster units). We chose hamlets with functional health posts due to the greater facility in mobilizing the population and corresponding logistical advantages. On the other hand, the census approach (within those clusters) was adopted because variations in the density of eligible children, estimated according to data from 24-10-2014 extracted from CISA’s HDSS database, was expected, and the real density in each cluster was needed.

### 3.2. Randomization

The hamlets will be considered as cluster units. For randomization, the names of the hamlets will be written down on pieces of paper and placed in a bag and then successively removed. The first two papers to be removed will be attributed to the Nutrition arm, the following two to the WASH/Malaria arm and the next pair to the control with this procedure repeated until there are no papers left in the bag. This process will be carried out by the two CISA researchers coordinating the study.

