## 1. Background

Anemia, especially severe anemia, is associated with increased child mortality rates [1]. Moreover, limitations in physical and cognitive development, leading to an increase in academic failure and susceptibility to infectious diseases, are also of great concern [1,2,3,4]. Regional studies conducted in the Dande municipality (Bengo province) reported a 57% prevalence of anemia in under-5 children, indicative of a severe public health problem [5]. In this setting, in addition to the expected association with undernutrition (responsible for nearly 13% of anemia cases), clusters of high risk of anemia were found to overlap with *Plasmodium falciparum* and *Schistosoma haematobium* risk zones (associated with 16% and 10% of the cases, respectively) [5,6].

Around half of anemia cases are estimated to result from Iron Deficiency (ID) [7]. However, in malaria endemic countries, routine iron supplementation remains controversial and is only undertaken with caution, as the practice has been associated with both an increased incidence and severity of malaria, especially in non-iron-deficient anemic people [8,9,10,11,12]. Additionally, single nutrient deficiencies are rare, as insufficient ingestion of other hematopoietic micronutrients may occur and cause nutritional anemia. On the other hand, the high prevalence, intensity, reinfection and incidence rates of anemia-related infections can also contribute to iron deficiency anemia, potentially refractory to iron supplementation [2,5,13,14,15,16].

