## 2. Materials and Methods

### 2.1. Study Setting

This study targets hamlets with functional primary health care facilities within CISA’s Dande HDSS study area [42]. The surveyed area is located in the Bengo Province (Dande municipality), and includes all the hamlets in the communes of Úcua, Caxito, Mabubas, as well as some hamlets in Kikabo and Barra do Dande [42]. Within this area, between 2010 and 2014, the total resident population varied between 63,081 and 58,645, with the percentage of under-5 children ranging from 17.7% to 13.9%. Additionally, the fertility rate varied between 4.8 and 3.7 births per woman, with the crude birth rate ranging from 40.4 to 24.2 live births/year/1000 people and the under-5 mortality rate fluctuating between 92.1 and 60.1 per 1000 live births [42]. As the entire population of Kikabo and Barra do Dande are not fully surveyed by the Dande HDSS, they will not be included in this study. Although 15 hamlets with health facilities are located within this area, only those providing daily primary care practices will be included in this study [43].

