### 2.2. Study Design

#### Baseline Assessment (Pre-Intervention Evaluation)

There were two qualitative pilot studies: (1) to characterize mother-to-child nutritional practices (as a basis to structure the questionnaire) and (2) to design a locally adequate Food Photography Atlas (FPA) for children U5 (for the 24 h recall evaluation). The first study was conducted between August and September of 2014 and enrolled 808 children aging 0–59 months and their caretakers in a two-stage cluster sampling strategy. Using a Portuguese translated questionnaire, adapted from ProPAN 14, we collected data on children’s breastfeeding, feeding practices and detailed food consumption in the previous 24 h [44]. As a result, data regarding the commonly consumed food was collected and a preliminary FPA S was produced. Following this, the second study, aiming at validating the previously mentioned FPA and to allow for the collection of age and context-specific food portion and nutrient ingestion among preschool children from the Bengo province, was conducted between February and March 2015. This was a convenient cross-sectional study that enrolled 75 primary caretaker residents in the Mabungo and Riceno hamlets within CISA’s study area. In sum, dishes were prepared according to local recipes, food photographs were produced, tested and selected, portion sizes were estimated and validated, and the reproducibility of this tool was evaluated. These results are being published elsewhere.

Using these tools, a pre-intervention evaluation, aiming to characterize the study population regarding anemia and its etiologic profile (by specific age groups (children aged under 6 months, between 6 and 23 months and between 24 and 36 months), will be performed.

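### The bag draw leaves control with the fewest or joint-fewest hamlets unless there are 6 or 12, and does nothing to balance a small number of hamlets on known risk

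*Protocol article*

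**What the plan says.** Section 3.2 makes the hamlet the unit ("The hamlets will be considered as cluster units") and sets the order of assignment: "The first two papers to be removed will be attributed to the Nutrition arm, the following two to the WASH/Malaria arm", then "the next pair to the control with this procedure repeated until there are no papers left in the bag". It gives no rule for an incomplete last cycle, and it describes no stratification, matching or constraint.

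Section 2.1 sets a ceiling on the number of hamlets but not the number itself: "Although 15 hamlets with health facilities are located within this area, only those providing daily primary care practices will be included in this study".

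On what is known about the hamlets, Section 1 reports that in this municipality "clusters of high risk of anemia were found to overlap with" malaria and urogenital schistosomiasis risk zones. Section 3.1 expects the density of eligible children to vary, using surveillance data already extracted. Section 2.2 plans a pre-intervention evaluation "aiming to characterize the study population regarding anemia and its etiologic profile". Section 2.3 adds: "Only children with pre-intervention evaluation will be allocated to the Randomized Controlled Trial (RCT".

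Section 6 accepts that randomization may leave confounding. The measures it offers are kits, training, monitoring and plausibility arguments, and none of them acts on the allocation.

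**The concern.** A fixed order repeated until the bag is empty gives any remainder to Nutrition first and to control last. Section 1.2 compares each education arm with control, so a small control arm weakens two of the three questions at once.

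Separately, with 15 hamlets at most, an unrestricted draw can put hamlets from the high-risk zones mostly in one arm. Malaria and schistosomiasis are causes of the primary outcomes (hemoglobin and anemia, Table 2) and direct targets of one arm. An imbalance on them would therefore blur the comparison that the trial is meant to make. Once the hamlets have been assigned, it can be adjusted for only in part.

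**Working it through.** The article states no sample size, power, intracluster correlation or final hamlet count, so there is no figure of its own to reproduce. The allocation rule can be followed exactly.

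**Arm sizes and precision.** Inputs: the order in Section 3.2 and a count of 6 to 15 hamlets. The ceiling of 15 is from Section 2.1; the floor of 6, one full cycle, is my choice. With equally informative hamlets, the variance of an arm-versus-control contrast is proportional to 1/n(arm) + 1/n(control). An even split, N/3 hamlets per arm, gives 6/N. This is a benchmark only, because it is not a whole number for every N. The ratio is the first factor divided by the second.

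| Hamlets | Nutrition/WASH/Control | Even split 6/N | Nutrition–control (ratio) | WASH–control (ratio) |
|---|---|---|---|---|
| 6 | 2/2/2 | 1.000 | 1.000 (1.00) | 1.000 (1.00) |
| 7 | 3/2/2 | 0.857 | 0.833 (0.97) | 1.000 (1.17) |
| 8 | 4/2/2 | 0.750 | 0.750 (1.00) | 1.000 (1.33) |
| 9 | 4/3/2 | 0.667 | 0.750 (1.12) | 0.833 (1.25) |
| 10 | 4/4/2 | 0.600 | 0.750 (1.25) | 0.750 (1.25) |
| 11 | 4/4/3 | 0.545 | 0.583 (1.07) | 0.583 (1.07) |
| 12 | 4/4/4 | 0.500 | 0.500 (1.00) | 0.500 (1.00) |
| 13 | 5/4/4 | 0.462 | 0.450 (0.97) | 0.500 (1.08) |
| 14 | 6/4/4 | 0.429 | 0.417 (0.97) | 0.500 (1.17) |
| 15 | 6/5/4 | 0.400 | 0.417 (1.04) | 0.450 (1.12) |

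Control is strictly smallest at 9, 10, 11 and 15. It ties with WASH/Malaria at 7, 8, 13 and 14, and all arms are equal at 6 and 12. Among the strictly-smallest counts, the loss peaks at 25%. At the tied counts, the Nutrition–control contrast loses nothing and the loss falls on WASH–control, where both arms are small (33% at 8 hamlets).

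**Chance imbalance at baseline.** The article gives no between-hamlet variation, so I assume a normal spread of true hamlet anemia prevalence with SD s of 0.05, 0.10 or 0.15. The Nutrition–control difference in mean hamlet prevalence then has SD s × √(1/n(Nutrition) + 1/n(control)). For 6 hamlets and s = 0.10 this is 0.10 × √1 = 0.10, so P(gap > 10 points) = P(|Z| > 1) = 0.32. For 15 hamlets it is 0.10 × √0.417 = 0.0645, so P(|Z| > 1.55) = 0.12. Simulation agrees:

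| Assumed SD | 6 hamlets | 9 | 12 | 15 |
|---|---|---|---|---|
| 0.05 | 0.045 | 0.021 | 0.004 | 0.002 |
| 0.10 | 0.32 | 0.25 | 0.16 | 0.12 |
| 0.15 | 0.50 | 0.44 | 0.35 | 0.30 |

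A second illustration assumes that one third of the hamlets are high-risk. The chance that control receives none of them is C(4,2)/C(6,2) = 6/15 = 0.40 with 6 hamlets, 35/84 = 0.42 with 9, 70/495 = 0.14 with 12 and 462/3003 = 0.15 with 15.

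**The case against.** The strongest reply is that the arm-size problem may not arise. The hamlet count is not given, the article condenses a fuller protocol, and 6 or 12 would be natural for drawing pairs over three arms. This stands as a condition: at 6 or 12, only the point about the unrestricted draw remains.

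The second reply is that simple cluster randomization is valid. Section 5.2 compares baseline with follow-up, and a primary outcome is the variation in hemoglobin, which absorbs part of a baseline difference. That also stands, in part. It limits the harm, but it recovers neither the precision lost to a small control arm nor balance on risks, such as malaria transmission, that go on acting during follow-up.

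A reader might infer more than the documents support:

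- **Control is always the least precise arm.** At tied counts it is no smaller than WASH/Malaria.
- **A 29% loss at 10 hamlets.** That compares 0.75 with 0.583, the factor under a 3/3/4 layout that favors control. Against an even split the loss is 25%, and 10 is the worst count for both contrasts together.
- **A floor on permutation p-values** (1/15 with 4 against 2 hamlets). Section 5.2 plans analysis of variance and logistic regression, not a permutation test.
- **Baseline results in hand at the draw.** Section 3.2 does not date the draw. Section 2.3 says which children enter the trial, which implies that the baseline evaluation comes first but does not say so. The risk mapping and surveillance density data existed in any case.
- **Eligible hamlets known to differ widely.** Section 1 describes zones in the municipality, not the hamlets with health posts.

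**Conclusion.** The point holds in a conditional form. As written, the rule puts control last in the queue for hamlets, which leaves it smallest or joint-smallest at eight of the ten counts from 6 to 15. The cost ranges from nothing at 6 or 12 to 25% extra variance on both control contrasts at 10, or about 12% in standard error (√1.25 = 1.12). At 11 it is about 7%.

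The unrestricted draw is unbiased in expectation. The risk is chance imbalance, which is negligible if hamlets differ little (SD 0.05 with 12 to 15 hamlets) and substantial if they differ more and are few (25% to 50% chance of a gap above 10 points with SD 0.10 to 0.15 and 6 to 9 hamlets). These probabilities rest on assumed SDs and the arm sizes on an unstated count, but the allocation rule is fixed in the text. It should be changed before the draw.

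**What to change.** 1. Close the list of qualifying hamlets before the draw and state the number.
2. Fix arm sizes in advance to differ by at most one, with the first extra hamlet going to control and any second one to an education arm chosen at random. In the order Nutrition/WASH/Control this gives, for example, 3/3/3 at 9, 3/3/4 at 10 and 5/5/5 at 15.
3. Draw at random from the allocations that are balanced on one or two hamlet-level variables: baseline anemia prevalence and number of children or, if the draw comes before the census, the existing risk-zone and surveillance data.
4. Account for the constraint in the analysis.

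With only six hamlets there are 6!/(2!2!2!) = 90 allocations. Use a light constraint on one variable and avoid matched triplets: two triplets leave four Nutrition–control arrangements within triplets, against six between the two arms in an unrestricted draw.

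The cost is a short script or stratified bags in place of one bag. The draw may have to wait until all hamlets have baseline data, and the constraint must be carried into the analysis.
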